### Recruitment and patient involvement

2.3

This study protocol was designed in collaboration with a special education school in Quito and a child neurodevelopment center in Riobamba. Both are private centers where autistic children and adolescents receive rehabilitation services. Additional participants will be recruited through posters and flyers distributed on social networks, at educational institutions, and through associations of autistic children’s parents. Children in Group B will be recruited from the family networks of Group A participants and matched for sex and age with their autistic peers. The target ratio between Groups A and B is approximately 1:2. During the development of the protocol, parents and professionals from recruitment sites provided valuable recommendations about the recruitment process, procedures and study goal.

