#### Group B - non-autistic children without neurodevelopmental disorders

2.2.2

This group will include children and adolescents aged 3 to 17 years (n = 100), from the general population with age and gender distribution similar to the autistic group.

*Inclusion criteria*

Age between 3 and 17 years.

*Exclusion criteria*

A 10-item Autism Spectrum Quotient (AQ-10) score of 6 points or higher.A Parent’s Observations of Social Interactions (POSI) score of 3 points or higher.History of diagnosis, therapy, or treatment for any neurodevelopmental disorder coded under ICD-10 F84.Inability to sit and/or stand independently.

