#### Sample size

2.2.4

The sample size was determined based on the expected difference in malnutrition prevalence between autistic children and their NA peers in a cross-sectional comparison. According to the *Encuesta Nacional de Salud y Nutrición* (24), 35% of the Ecuadorian children younger than 11 years of age are overweight or obese, while among adolescents the prevalence of overweight or obesity is 30%. The prevalence of extreme thinness is 2% among Ecuadorian children and adolescents. Based on these figures, we assumed an approximate malnutrition prevalence of 37% in the NA population.

There is no published data on prevalence of malnutrition in Ecuadorian autistic children up to date. To estimate this value, we referred to data from a recent study in another Latin American country (Mexico), which reported a malnutrition prevalence of 57.50% among autistic children (45% obese/overweight, and 12.50% underweight) (25). To estimate the sample size required to detect this difference (~20.50%) between the groups, we used the formula for comparing two independent proportions in a two-sided hypothesis test (26):

$n=\frac{{\left(Z_{\alpha /2}+Z_{\beta }\right)}^{2}\times [p_{1}(1-p_{1})+p_{2}(1-p_{2})]}{{\left(p_{1}-p_{2}\right)}^{2}}$, where:

$Z_{\alpha /2}$ = 1.96 (corresponding to a 95% confidence level),

$Z_{\beta }$ = 0.84 (corresponding to 80% power),

$p_{1}$ = 0.57 (estimated malnutrition prevalence in autistic children - Group A),

$p_{2}$ = 0.37 (estimated malnutrition prevalence in NA children - Group B).

The formula yields an approximate sample size of 94 participants per group. To account for a projected non-response rate of 5%, the sample size increases to 100 participants per group. This sample size is also adequate for detecting large effect sizes in secondary comparisons, such as the prevalence of SMD, which has been reported to be between 81.50% and 95.00% among autistic children and may reach 16.50% in children of the population (7, 18, 27). Thus, our sample will be sufficient for the validation of the neurometric test, achieving a statistical power close to 1.

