#### Analysis of the relation between exposures and outcomes

3.6.2

In all analyses, the researchers will blind the identity of the comparison groups. Statistical analysis will be performed using multilevel mixed-effects linear and nonlinear models in R Studio and Python (56). These models offer several advantages over standard parametric and non-parametric tests: they are more robust to violations of normality, which is common in biological data, and they do not require homoscedasticity (57, 58). Additionally, they accommodate the nested structure of our data (trials nested within sessions, sessions nested within participants, participants nested within groups) and handle missing data more effectively than repeated-measures ANOVA. Normality of residuals will be assessed visually with quantile-quantile (Q-Q) plots and statistically using the Shapiro–Wilk test; homoscedasticity will be evaluated with the Breusch–Pagan test (59, 60). Data will be considered statistically significant at a p-value < 0.05. Given the large number of variables related to diet, nutritional status, ASD severity, and sensorimotor integration, exploratory analyses will include the Kruskal–Wallis test to compare groups on non-normally distributed variables (61). In addition, cluster analysis (k-means clustering and equivalent algorithms) will be used to identify profiles of gut microbiota or dietary patterns (62).

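### Group B is described both as a general-population sample and as family-network controls matched to Group A, while the sample size and the stated model structure treat all children as independent

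*Protocol article*

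**What the plan says.** All references are to the protocol article.

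- **Source of Group B, section 2.2.2:** the children come "from the general population with age and gender distribution similar to the autistic group".
- **Source of Group B, section 2.3:** "Children in Group B will be recruited from the family networks of Group A participants". Each is to be paired by sex and age. The degree of kinship and whether a household is shared are not stated.
- **Sample size, section 2.2.4:** the A versus B comparison uses "the formula for comparing two independent proportions in a two-sided hypothesis test", with prevalences of 0.57 (Group A) and 0.37 (Group B). The 0.37 is built from national survey figures: 35% overweight or obese plus 2% extreme thinness.
- **Model structure, section 3.6.2:** the hierarchy is "trials nested within sessions, sessions nested within participants, participants nested within groups". No family or matched-set level appears. The same section says of mixed models that "they do not require homoscedasticity", and plans a Breusch–Pagan test without stating what follows from it.
- **Other tests:** section 3.6.1 names PERMANOVA and the Wilcoxon rank sum test, and section 3.6.2 adds Kruskal–Wallis. None is described as accounting for linked children.
- **Limitations, section 4.2:** recruitment through private centres is discussed; family-network controls are not.

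**The concern.** A general-population sample and a family-network sample are different control groups. The outcomes here are nutritional status, diet and gut microbiota, which children in one kin network, and above all in one household, may share. Three consequences follow.

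1. Linked children are not independent, so standard errors computed as if they were are wrong whenever the within-family correlation is not zero. The direction depends on the contrast.
2. The control prevalence used for sizing describes a population other than the one section 2.3 recruits from.
3. If A and B turn out alike, a reader cannot tell whether autism makes no difference or whether the controls share the cases' environment, unless the linkage was recorded.

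The homoscedasticity sentence is a separate inaccuracy in the same section. A standard linear mixed model assumes constant residual variance unless a variance structure or robust standard errors are specified.

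**Working it through.** **Inputs from section 2.2.4:** p1 = 0.57, p2 = 0.37, z = 1.96 and 0.84, 5% non-response. **Assumed, because the article gives no figure:** within-family correlation ρ from 0.1 to 0.5; prevalence in family-network controls from 0.40 to 0.45. Power is taken at 95 analysable children per group (100 less 5%).

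**Step 1: the plan's own figure.** (1.96 + 0.84)² × [0.57×0.43 + 0.37×0.63] / 0.20² = 7.84 × 0.4782 / 0.04 = 93.7, so 94. Then 94/0.95 = 98.9, so 99, which the plan rounds to 100. The arithmetic reproduces.

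**Step 2: dependence alone, A versus B.** For 1:1 linked pairs the variance of the difference is [p1q1 + p2q2 − 2ρ√(p1q1·p2q2)]/n. At ρ = 0.3 the numerator is 0.4782 − 0.6×0.2390 = 0.3348, so true SE / independence SE = √(0.3348/0.4782) = 0.84.

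| ρ (assumed) | True SE / independence SE | True alpha, unpaired test | Power, unpaired | Power, paired |
|---|---|---|---|---|
| 0.1 | 0.95 | 0.039 | 82% | 84% |
| 0.2 | 0.89 | 0.028 | 83% | 88% |
| 0.3 | 0.84 | 0.019 | 85% | 92% |
| 0.5 | 0.71 | 0.006 | 89% | 98% |

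The ratio is close to √(1−ρ). It is the same with two controls per autistic child, since 1 + (1+ρ)/2 − 2ρ = 1.5(1−ρ) against 1.5 under independence. This matters because section 2.3 also mentions an A-to-B ratio of about 1:2.

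The sign reverses only for relatedness inside one group. If Group B were made of sibling pairs unrelated to Group A, true / independence SE = √((2+ρ)/2), or 1.02 to 1.12 for ρ of 0.1 to 0.5. The SE would then be 2% to 11% too small.

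**Step 3: pooled associations (objective 4).** For linked pairs the approximate design effect is 1 + ρx·ρy, where ρx and ρy are the within-family correlations of covariate and outcome.
- Covariate constant within a family, such as a household socioeconomic score for children sharing the household: ρx = 1, ρy = 0.3, design effect 1.3, stated / true SE = 1/√1.3 = 0.88, so about 12% too small.
- Child-level covariate, such as a startle measure: ρy = 0.3 and ρx = 0.1 to 0.5, design effect 1.03 to 1.15, so about 1.5% to 7% too small.

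Group C is not described as family-recruited, which dilutes both.

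**Step 4: a different control prevalence, independence kept.** Power = Φ(d/√([p1q1 + p2q2]/95) − 1.96), with d = p1 − p2.

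| p2 (assumed, except 0.37) | d | Power at 95 per group | n per group for 80% |
|---|---|---|---|
| 0.37 (plan) | 0.20 | 80% | 94 |
| 0.40 | 0.17 | 66% | 132 |
| 0.41 | 0.16 | 61% | 150 |
| 0.43 | 0.14 | 50% | 197 |
| 0.45 | 0.12 | 38% | 269 |

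Check at 0.40: 0.17/√(0.4851/95) = 2.379; 2.379 − 1.96 = 0.419; Φ = 0.66.

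**Step 5: both together.** At p2 = 0.41 and ρ = 0.2, power is 62% unpaired and 70% paired. Using the link recovers part of the loss, not all of it.

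**The case against.** The article is a condensed protocol, and the exact random-effects structure could be left to a full plan. Age and sex matching is largely covered because both are covariates. Sharing an environment also controls confounding, so a smaller A–B difference is not in itself bias. For A versus B the independence analysis errs on the safe side, and at the planned prevalences its power stays at or above 80%. All of this stands. It does not remove the conflict over where Group B comes from, or the fact that section 3.6.2 does spell out a hierarchy and omits the level that section 2.3 creates.

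Four stronger readings are tempting and not supported:

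- **That the contrast is attenuated.** A reader might infer this from the recruitment route. The article does not define family networks and gives no prevalence for such controls; siblings and cousins are only one reading.
- **That the linkage produces false positives for A versus B.** With links running between A and B the effect is the reverse.
- **That group will be a random effect with three levels.** The nesting phrase describes the data structure while motivating mixed models. The abstract's adjusted regressions for group comparisons point to group as a fixed term. Clearer wording is enough.
- **That the homoscedasticity sentence implies a known type I error.** For 100 versus 200 children with a pooled variance, an SD ratio of 1.5 to 2 gives 8.5% to 11%. The ratio is unsupported by the article, and the calculation pools B with C. At 100 versus 100 the error is about 5%. The sizing endpoint is binary and has no such residual variance.

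**Conclusion.** The concern holds in a limited form. The two descriptions of Group B conflict, the sizing and the stated hierarchy ignore the family link, and the control prevalence is a national figure for a population that section 2.3 does not sample directly.

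The standard-error problem is moderate. For A versus B it is conservative and costs precision (true SE 0.95 to 0.71 of the independence value at assumed ρ of 0.1 to 0.5). For pooled associations it is mildly anti-conservative (at most about 12% at assumed ρ of 0.3, less for child-level covariates). Dependence alone does not undermine the sample size.

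The risk to power comes only from the planning prevalence: about 66% to 38% if family-network controls have 0.40 to 0.45. That range is an assumption. The A versus C comparison is not affected in the same way. The homoscedasticity statement is wrong as a general claim, but its effect cannot be sized from the article.

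**What to change.** - **Sections 2.2.2 and 2.3:** give one consistent description of where Group B comes from.
- **Data collection:** record a family or matched-set identifier and whether the household is shared. This is best done at enrolment, before de-identification.
- **Section 3.6.2:** state that group is a fixed three-level factor, and add a random intercept for family or matched set, or use family-clustered robust standard errors.
- **Section 3.6.1:** use family-restricted permutations for PERMANOVA only as a sensitivity analysis of A versus B among linked children. They cannot serve the whole sample, because Group C and children with no enrolled relative have no family set.
- **Section 2.2.4:** say that 0.37 is a national figure and show power over an assumed range, for example 0.37 to 0.45.
- **Section 4.2:** list family-network controls as a limitation.
- **Separately, section 3.6.2:** withdraw the homoscedasticity claim and plan group-specific residual variances or robust standard errors for continuous outcomes.

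The cost is some wording, one identifier, one question to caregivers and a few lines of model code. The single power figure becomes a range.

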### Procedures

2.4

Data will be collected through three ~60-minute visits conducted at participants’ homes or preferred locations by trained researchers (including medical professionals). All personnel will receive standardized training in instrument administration, pediatric assessment protocols, and transcription procedures. A summary of visits is depicted in **Table 1**.

**Table 1 T1:** Summary of study visits and procedures.

Visit	Procedures conducted	Measurements/tools used
Visit 1	- Informed consent - Sociodemographic/clinical data - First dietary assessment - Autism screening - Handing out stool sample collection kits	- Questionnaires - CARS (group A) - POSI/AQ-10 (all groups) - 24-HDR
Visit 2	- First neurobehavioral assessment - Anthropometry/bioimpedance - First dietary assessment	- Smartphone application - Stadiometer, InBody120 - 24-HDR
Visit 3	- Second neurobehavioral assessment - First dietary assessment - Stool sample collection - Completion of pending data	- Smartphone application - 24-HDR

24HDR, 24-hour dietary recall; AQ-10, 10-item Autism Spectrum Quotient; CARS, Childhood Autism Rating Scale; POSI, Parent’s Observations of Social Interactions.

The following data will be collected:

Sociodemographic and medical information: Personal data will be collected using a customized questionnaire (Annex1). Socioeconomic status information will be obtained using the *Encuesta de Estratificación del Nivel Socioeconómico*, elaborated by the *Instituto Ecuatoriano de Estadísticas y Censos* (Annex 2). General health status, treatments, and therapies will be documented using caregiver-directed questionnaires (Annex 3).Nutritional assessment: Dietary patterns will be assessed through three 24-hour dietary recall (24-HDR) assessments on three non-consecutive days (Annex 4 of the **Supplementary Material**). Nutritional status will be evaluated via anthropometric measurements and body composition analysis using bioelectrical impedance, documented in a technical sheet (Annex 5 of the **Supplementary Material**). Caregiver and healthcare professional perceptions regarding nutrition will be captured through semi-structured interviews (Annex 6 of the **Supplementary Material**).Neuropsychological assessment: Autism symptom screening will be conducted using screening tools for different ages: children <4 years will be assessed using the POSI (Annex 7 of the **Supplementary Material**), those ages 4–11 years with the AQ-10 child version (Annex 8 of the **Supplementary Material**), and those ages >11 years with the AQ-10 adolescent version (Annex 9 of the **Supplementary Material**). Symptom severity will be evaluated exclusively in Group A using the Childhood Autism Rating Scale (CARS) (Annex 10 of the **Supplementary Material**).Neurophysiological Assessment: Sensorimotor integration differences will be assessed using a smartphone application.GM analysis: The composition and diversity of the GM will be analyzed through stool sample collection and bacterial DNA sequencing.

The initial session will involve obtaining informed consent, collecting baseline sociodemographic information, health status, treatments/therapies, and conducting the first 24-HDR. CARS and autism screening questionnaires (POSI, AQ-10) will be administered concurrently. Caregivers will receive stool collection kits with instructions; child presence is optional. During the second session, children will undergo the first neurobehavioral assessment (15–20 minutes), comprehensive anthropometric measurements, body composition evaluation, and the second 24-HDR. The third session will include another neurobehavioral assessment, the final 24-HDR, and stool sample collection. Any outstanding data will be collected in the last session.

Throughout the study, caregivers may contact researchers for clarification and will have the option to complete questionnaires remotely. All participants retain the right to withdraw at any time without penalty. Following the study’s completion, caregivers will receive individualized reports on their child’s nutritional status, along with a summary of the aggregate study results. All materials will be presented in an accessible format and in Spanish.

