#### Sociodemographic and medical information

3.5.1

Sociodemographic and clinical data will be collected through a customized survey directed to the caregivers. The variables include age, sex assigned at birth, socioeconomic position, medication use, and general health status. Age will be recorded in years and months, calculated as the time elapsed from birth to the date of the first interview with the field researchers.

The socioeconomic position of children will be evaluated using a previously described instrument (28). Briefly, the instrument evaluates six dimensions: (i) Housing characteristics; (ii) access to technology; (iii) possession of material goods; (iv) consumption habits; (v) level of education of the head of the household; and (vi) household income. The sum of the scores for all questions ranges from 0 to 1000. According to this score, households are classified into five socioeconomic groups: A (>845), high; B (>696 and ≤ 845), upper-middle; C+ (>535 and ≤ 696), middle; C− (>316 and ≤535), lower-middle; and D (≤316), low.

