#### Microbiota assessment

3.5.5

For stool sample collection from children, parents will be provided with faecal collection containers and instructed to collect the sample immediately before delivery. Instructions for the parents will be provided in written format with animated graphics (Annex 11 of the **Supplementary Material**). Stool samples will be collected in an OMNIgene•GUT OM-200 (DNA Genotek Inc.; Ottawa, Canada) or a DANASTOOL (Danagen; Barcelona, Spain) tubes and transported to the laboratory facilities for their subsequent storage at -80 °C until further analysis.

The GM composition of all participants will be characterized through gene marker amplification and sequencing, which is a highly accurate and specific approach for profiling microbial communities. GM analysis will be performed as reported previously with a few modifications detailed in Annex 12 of the **Supplementary Material** (46). Briefly, this analysis will comprise four steps: DNA extraction, library preparation, sequencing and bioinformatics.

Genomic DNA (gDNA) will be extracted and purified from stool samples using a bead-beating-based approach. Library preparation will involve a PCR-amplification of the 16S rRNA V3 region, followed by the attachment of dual index barcode adapters. The indexed DNA will then be sequenced in paired-end reads of 300 bp using the Illumina MiSeq Platform. Finally, bioinformatics analysis will be performed using the DADA2 protocol (46, 47). Differences within (alpha-diversity) and between (beta-diversity) groups will be assessed using QIIME2 (48). Alpha-diversity will be quantified by Shannon diversity index, whereas beta-diversity will be evaluated using principal coordinate analysis based on Bray–Curtis dissimilarity matrices (49, 50).

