Self-medication represents an important limitation that our study will address. In Ecuador, self-medication, particularly with antibiotics, is common across various demographic groups (75). Excluding participants based on reported medication use would severely constrain recruitment. We will therefore account for this potential confounder by adjusting for medication use in multivariable statistical models when examining associations between gut microbiota composition and other outcomes. Specifically, medication use will be included as a covariate in linear models for alpha-diversity analyses and in PERMANOVA for beta-diversity comparisons. Finally, following previously used approaches (76), we will evaluate the robustness of our findings through sensitivity analyses that leverage the detailed medication data collected, exploring drug dosage, the specific reason for medication, and the prescribing source.

Another potential limitation of our study is that no formal cognitive ability assessment will be conducted. Cognitive level can influence dietary patterns independently of sensorimotor differences, for example, by affecting a child’s ability to express food preferences or aversions. Moreover, 30–40% of children with ASD also have co-occurring intellectual disability, a rate substantially higher than among NA peers (77). To address this potential confounding, we will use CARS scores as a proxy for phenotypic severity within the ASD group. Although CARS does not measure cognitive ability directly, it correlates with functional impairment and will allow us to explore whether associations differ by severity level. Nevertheless, residual confounding by unmeasured cognitive differences cannot be entirely ruled out.

The broad age range (3–17 years) of our sample represents another limitation, given the significant developmental heterogeneity within this period. While a narrower range would reduce variability, it would also compromise sample size and generalizability. To address this, age will be included as a covariate in all multivariate models to adjust for its potential confounding effects. Additionally, we have selected age-appropriate instruments to ensure that measurements are sensitive to developmental stages. Nevertheless, residual age-related variability may still influence our findings, and we acknowledge this trade-off.

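### Medication use is scheduled at Visit 1 and stool at Visit 3 with no update between, so the microbiota adjustment may miss antibiotic courses started in the interval

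*Protocol article*

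**What the plan says.** Section 2.4 (Procedures) sets the order of measurement. For the first visit: "The initial session will involve obtaining informed consent, collecting baseline sociodemographic information, health status, treatments/therapies, and conducting the first 24-HDR". For the third: "The third session will include another neurobehavioral assessment, the final 24-HDR, and stool sample collection". Table 1 agrees: it lists clinical data under Visit 1 only and stool collection under Visit 3, and shows no medication item at Visit 2 or Visit 3. The only catch-all is at the end: "Any outstanding data will be collected in the last session".

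Section 3.5.1 makes medication part of the caregiver survey: "The variables include age, sex assigned at birth, socioeconomic position, medication use, and general health status". Section 2.4 assigns treatments to the Annex 3 questionnaire, which is not shown. Under section 3.5.5 parents are "instructed to collect the sample immediately before delivery", so the stool reflects exposure up to the day of hand-over.

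Section 4.2 (Study limitations) explains why this matters: "In Ecuador, self-medication, particularly with antibiotics, is common across various demographic groups". It declines to exclude on medication because recruitment would suffer, and commits to adjustment instead: "medication use will be included as a covariate in linear models for alpha-diversity analyses and in PERMANOVA for beta-diversity comparisons". The sensitivity analyses named there cover dose, reason and prescribing source.

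**The concern.** A covariate can adjust only for exposure that it records. Here the record is scheduled before the sample that it is meant to explain. A course started after the questionnaire and before the stool is among the exposures closest to the sample, and no look-back period asked at Visit 1 can capture it.

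Comparing the microbiota of autistic and non-autistic children is one of the study's specific aims. The eligibility criteria contain no medication exclusion, so control of antibiotic exposure rests on this covariate. The listed sensitivity analyses would not repair a missed course: they draw on the same medication data, and timing relative to the sample is not among the features they explore. The result would be incomplete adjustment in the alpha- and beta-diversity comparisons.

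**Working it through.** The article states no figure on this point, so there is none to reproduce. The check has two parts.

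**1. The schedule**

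| Item | Where scheduled | Source |
|---|---|---|
| Health status, treatments/therapies | Visit 1 | 2.4 text; Table 1 (clinical data) |
| Stool sample | Visit 3, taken just before hand-over | 2.4 text; Table 1; 3.5.5 |
| Medication update at Visit 2 or 3 | None listed | 2.4 text; Table 1 |
| Maximum Visit 1 to Visit 3 interval | None stated | 2.4 |

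The minimum interval can be inferred. Each visit carries one dietary recall. Section 2.4 requires three non-consecutive recall days, and section 3.5.3.3 requires two weekdays and one weekend day. A Thursday, Saturday and Monday pattern meets both, so the shortest gap is about 4 days.

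**2. How many children could be affected**

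Inputs:
- Total sample: 3 groups of 100 = 300 children (article).
- Antibiotic courses per child-year: 0.5, 1 or 2 (assumption; the article says only that use is common).
- Gap from Visit 1 to Visit 3: 4, 14 or 30 days (4 is the inferred minimum; the others are assumptions).

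With courses starting at a constant rate, the share of children starting at least one in the gap is 1 − exp(−rate × gap / 365.25). For 1 course per year and 14 days this is 1 − exp(−1 × 14 / 365.25) = 0.0376, and 300 × 0.0376 = 11.3.

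| Gap | 0.5 per year | 1 per year | 2 per year |
|---|---|---|---|
| 4 days | 0.5% (1.6 of 300) | 1.1% (3.3) | 2.2% (6.5) |
| 14 days | 1.9% (5.7) | 3.8% (11.3) | 7.4% (22.1) |
| 30 days | 4.0% (12.1) | 7.9% (23.7) | 15.1% (45.4) |

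These counts are children who start a course in the gap. The number actually missed is no larger than this and may be smaller, because a questionnaire completed late could record some of the courses.

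**The case against.** The strongest reply is that the article is a condensed account. Annex 3 (treatments) and Annex 11 (stool instructions) are not shown, and one of them may ask about recent antibiotics at hand-over. Section 4.2 describes detailed medication data, including dose and source, so the instrument is more than a yes/no item. Section 2.4 also lets caregivers complete questionnaires remotely and collects outstanding items at the last visit, so some medication records may be completed close to the stool sample. If the visits are only days apart, few children are affected.

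Part of this stands. That medication is recorded only once is a reading of the schedule, not a statement in it, and late completion may capture some later use. But a form already completed at Visit 1 is not outstanding, and remote completion does not tie the answer to the sample date. The order of measurement is published in both the text and Table 1, and neither describes an update.

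Three stronger readings are tempting, and the article does not support them:
- *That missed courses are entered as no use.* No coding rule for medication is given, and a child taking another drug might already count as a user.
- *That the gap would produce a false autism effect.* This needs treatment between visits to differ by group, and nothing in the article indicates that it does. If missed courses are few and similar across groups, the consequence is mainly noise and weaker adjustment.
- *That the startle outcomes are compromised in the same way.* The article adjusts for medication generally, but the problem it describes is antibiotics and the gut microbiota. It offers no basis for a comparable effect of short courses on the startle measures.

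**Conclusion.** The point holds as a limited weakness in the measurement schedule. As published, medication is scheduled at Visit 1, stool at Visit 3, no update is described and the interval has no upper limit. Courses started between the questionnaire and the sample may be missed by the covariate on which the microbiota analyses rely. Courses taken before or during Visit 1 can still be captured.

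The size cannot be fixed from the article. At an assumed 0.5 to 2 courses per child-year it is about 2 to 7 of 300 children with a 4-day gap, 6 to 22 with 14 days and 12 to 45 with 30 days. That is minor if visits are days apart and material if they are weeks apart. The article does not say which applies. An unseen annex may already close part of the gap.

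**What to change.** At stool hand-over at Visit 3, re-ask the Annex 3 medication items and record the date of the last antibiotic dose. Define the medication covariate in the alpha-diversity models and in PERMANOVA relative to the stool sample date, for example as time since the last antibiotic dose, instead of relative to the Visit 1 questionnaire. If an annex already does this, a sentence in Procedures and an entry under Visit 3 in Table 1 would settle the point.

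The cost is a few extra questions and one date field in REDCap at a visit that already takes place. No extra visit, staff or test is needed. It is best done before data collection begins, because dates of self-medication without a prescription are hard to reconstruct later.
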